#### The hypotheses to be tested are

**1**: The IYP will be safe, acceptable and feasible: at least 80% of subjects will complete the IYP.

**2**: Following the IYP, participants will show significant improvement on the primary outcomes of general functioning, arthritis functioning and HRQOL relative to controls. The benefits will be apparent post-treatment and at two-month follow-up.

**3**: Following the IYP, participants will report significant improvement on the secondary outcomes of pain, DAS28, and mood compared to controls. These improvements will be evident at both post-treatment and at two-month follow-up.

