#### Phase three (18 Months)

In this final phase, IY teachers will administer the IYP using the revised manual to 70 participants who will be assigned to either treatment (n = 35) or usual care control (n = 35). The controls will be immediately assigned to IYP at the end of the control phase (see Figure 2).

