### Design

A randomized control trial (RCT) design will be used to examine the impact of IYP for adolescents and young adults aged 16-35 years with RA on the primary outcomes of general and arthritis-specific functioning, and the secondary outcomes of DAS28, pain and mood.

The overall design of the study is depicted in Figure 2 below. After participants have completed the telephone screening and meet the study's eligibility criteria, they will be randomized into the IYP or usual care control group. All participants will be asked to fill out consent forms before their initial medical assessment, which includes a phlebotomy, measurement of blood pressure/resting heart rate, and a joint count conducted by a physician who will be kept unaware of group assignment. Before the medical assessment, a research assistant will send a link to the questionnaires for participants who choose to complete them online. A hard copy of the questionnaires will be taken to the medical assessment if the participant chooses to complete the paper-based version in a private medical office.

Those assigned to the IYP will then engage in the 6-week program; they will repeat the baseline assessments immediately following treatment and again at a two-month follow-up. Patients initially assigned to the wait-list group will continue their usual care. Both the yoga and control groups will either receive weekly phone calls or e-mails to monitor symptoms, medication use and physical activity. After 6 weeks, control participants will be re-assessed to ensure that they still meet study eligibility criteria; those that continue to meet criteria will then take part in the IYP. Following the IYP, participants will then repeat the baseline assessments at post-treatment and two-month follow-up.

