### Primary analyses

To test ***Hypothesis 2***: Participants in the IYP will demonstrate significantly greater improvement in HRQOL and functioning compared to controls. The primary outcomes include the SF-36, PDI and the HAQ. Two sets of analyses will be conducted. The first set of analyses will compare the initial yoga and control groups immediately after the IYP and control phase, respectively. Separate mixed group (yoga vs. control) by time (baseline vs. post-treatment/post-control) repeated measure analysis of variance (ANOVA) will be conducted on the primary outcomes, or the non-parametric equivalent (Friedman procedure), in the event the assumptions for parametric analyses are not met. We will use the Tukey-Fisher criteria for post hoc mean/median comparisons under the ANOVA or Friedman model. Consistent with ***Hypothesis 2***, we expect a group by time interaction wherein the yoga group will report improved functioning from baseline to post-treatment compared to the control group. The second set of analyses will assess maintenance of treatment gains during the follow-up period. If yoga and control groups do not differ significantly on SF-36, PDI and HAQ scores at baseline, then data from the two groups will be combined in order to maximize power. If groups differ at baseline, each group will be analyzed separately. Changes in SF-36, PDI and HAQ scores across baseline, post-treatment and follow-up will be evaluated using separate within-group repeated measures ANOVAs; Friedman's procedure will be used if parametric assumptions are not met. Consistent with ***Hypothesis 2***, we expect significant improvements in functioning scores from baseline to post-treatment, persisting at follow-up.

We will also conduct an ***intent-to-treat (ITT) analysis***on primary outcomes to confirm our findings in completers by including all participants who enrolled in the study, using the last observation carry forward approach. Participants who drop out will be included in the analysis by utilizing outcome scores before attrition.

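### Hypotheses 2 and 3 claim benefit over controls at two months, but controls start yoga at six weeks and the follow-up test is an uncontrolled, usually pooled, within-group ANOVA

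*Protocol article*

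**What the plan says.** All references are to the protocol article.

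- **Hypotheses.** For Hypothesis 2, the section listing the hypotheses says "participants will show significant improvement on the primary outcomes of general functioning, arthritis functioning and HRQOL relative to controls", and the next sentence reads "The benefits will be apparent post-treatment and at two-month follow-up". For Hypothesis 3 it says "participants will report significant improvement on the secondary outcomes of pain, DAS28, and mood compared to controls", again at both time points.
- **Crossover.** Phase three states: "The controls will be immediately assigned to IYP at the end of the control phase". The Design section adds a condition. Controls are re-assessed for eligibility after six weeks, and "those that continue to meet criteria will then take part in the IYP".
- **Six-week analysis.** Primary analyses specifies a group-by-time ANOVA with two time points, baseline and the end of the yoga or control period. This is the only yoga-versus-control test.
- **Follow-up analysis.** The same section, under the test of Hypothesis 2, continues: "Changes in SF-36, PDI and HAQ scores across baseline, post-treatment and follow-up will be evaluated using separate within-group repeated measures ANOVAs". If the arms "do not differ significantly on SF-36, PDI and HAQ scores at baseline, then data from the two groups will be combined"; otherwise each arm is analysed alone. Secondary analyses applies the same within-group approach to Hypothesis 3.

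**The concern.** A claim of benefit over controls needs controls at the time of the claim. By the two-month visit of the yoga arm, the wait-list arm has been offered, and largely completed, the same programme. The follow-up ANOVA tests whether scores differ across visits. It cannot separate a yoga effect from natural course, regression to the mean, expectation or repeated testing. Entry requires five or more tender joints, five or more swollen joints and a further sign of activity, so some improvement without any treatment effect is to be expected. That is most direct for DAS28 and less direct for the questionnaires.

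Pooling adds two problems. First, a non-significant difference at study entry says nothing about whether pooled pre-post change is a valid measure of the yoga effect. Second, study entry in the wait-list arm lies six weeks before yoga begins. If the eligibility re-check is applied as the Design section describes, the wait-list half of the pooled sample is also selected after randomisation on disease that has stayed active.

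The article says the results are meant to prepare a larger trial. A false signal of durable benefit would carry over into its planning.

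**Working it through.** **1. Who is untreated at the two-month visit?**

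| Weeks from start | Yoga arm | Wait-list arm |
|---|---|---|
| 0 to 6 | yoga | usual care |
| 6 | post-treatment visit | re-assessment, then yoga starts |
| about 12 | follow-up period | yoga ends |
| about 14 to 15 (6 weeks + 2 months) | follow-up visit | 2 to 3 weeks after its own yoga |

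No untreated group exists at weeks 14 to 15.

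**2. Does any planned test compare the arms then?** The group-by-time ANOVA stops at six weeks. Both branches of the follow-up analysis, pooled or arm by arm, are within-group. So the two-month half of Hypotheses 2 and 3 has no test that matches its wording.

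**3. The plan's own numbers.** 35 per arm × (1 − 0.20) = 28 completers, which agrees with the article; pooled, 2 × 28 = 56. The article's sample size of 27 per arm is for the six-week interaction and does not bear on this point. The re-check could bring the pooled number below 56.

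**4. How often would the follow-up test be significant with no yoga effect?** The documents give neither the non-specific improvement δ (in SD units) nor the correlation ρ between visits, so both are assumptions. For baseline versus follow-up by paired t-test, two-sided 0.05:

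- standardised change: dz = δ / √(2(1 − ρ))
- noncentrality: dz × √n, with n = 56 and critical t(55) = 2.004
- example, δ = 0.2 and ρ = 0.7: dz = 0.2 / √0.6 = 0.258; noncentrality = 0.258 × 7.483 = 1.93; probability 0.476

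| δ | ρ = 0.5 | ρ = 0.7 | ρ = 0.8 |
|---|---|---|---|
| 0.2, n = 56 | 31% | 48% | 64% |
| 0.3, n = 56 | 60% | 81% | 94% |
| 0.2, n = 28 (one arm) | 17% | 26% | 37% |
| 0.3, n = 28 (one arm) | 33% | 51% | 68% |

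The planned three-visit ANOVA was simulated with 20,000 runs per setting, equal correlations, and the shift δ present at both later visits. With n = 56 it gives 32%, 49% and 68% for δ = 0.2, and 62%, 85% and 96% for δ = 0.3. With δ = 0 it gives 5%, as it should. The paired-t figures are therefore slightly conservative for the test actually planned.

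**5. The pooling gate.** Under valid randomisation, with three independent baseline tests at 0.05, the chance of at least one significant result is 1 − 0.95³ = 0.143. If the three outcomes correlate at 0.5 to 0.7, it is about 12% to 11%. Chance alone thus decides in roughly one trial in eight whether the arms are pooled. SF-36 yields eight scales, so the number of tests could be larger than three.

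**6. Which baseline for the wait-list arm?** Primary analyses does not say. With study entry, six untreated weeks are counted as yoga change. With the pre-yoga re-assessment, that period is removed, but the baseline visit is then also the visit at which eligibility was re-checked. The bias runs differently in the two cases, and the documents do not allow its size to be given.

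**The case against.** The strongest reply is that the analysis sections already keep the two claims apart. They present the follow-up analysis as a check that gains persist, and Secondary analyses ties the comparison with controls to the six-week period. On that reading the fault is a wording mismatch with the list of hypotheses, in a self-described exploratory pilot whose randomised comparison is sound. This stands in part. The six-week test is untouched, and a within-person description of persistence is legitimate if labelled as such. But the follow-up ANOVA is set out under the test of Hypothesis 2, and the hypothesis reads "relative to controls. The benefits will be apparent post-treatment and at two-month follow-up". Hypothesis 3 has the same form. The passages conflict, and a different analysis could not resolve it because the design has no comparator at that visit.

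Other objections also have weight:

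- The drift and correlation values are assumptions. Nobody is selected on SF-36, PDI or HAQ, and medication is expected to be stable, so regression to the mean on the primary outcomes is indirect.
- If yoga truly had no effect, the six-week test reported alongside would usually be null.
- Both branches of the pooling gate are uncontrolled, so the gate is a side issue.
- The sections differ on how strictly the six-week re-check is applied: Phase three and Treatment administration state no such condition. The selection effect may be smaller than feared.
- Using the pre-yoga visit as the wait-list baseline does not remove regression to the mean, and the immediate-yoga arm was itself selected on active disease at entry.

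None of these restores a controlled comparison at two months. They are reasons to label the follow-up result as uncontrolled.

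**Conclusion.** The concern holds. The two-month half of Hypotheses 2 and 3 cannot be tested as worded. This follows from the crossover and the planned analyses and rests on no assumption. The size of the risk does rest on assumptions: with no yoga effect, n = 56 and a non-specific improvement of 0.2 to 0.3 SD, the paired test would be significant in 31% to 94% of trials across correlations of 0.5 to 0.8 (48% and 81% at 0.7), against a nominal 5%. Regression to the mean, the gate and the selection at re-check are supporting points. Because half of each of the two efficacy hypotheses is affected, this should be corrected before the data are analysed.

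**What to change.** 1. In Hypotheses 2 and 3, limit the comparison with controls to the post-treatment (six-week) assessment.
2. Restate the two-month part as an uncontrolled within-person change from baseline, reported as an estimate with a 95% confidence interval and not offered as evidence of efficacy over controls.
3. Lead with the immediate-yoga arm, which has not passed through the six-week re-check and has no untreated interval before yoga.
4. If a pooled analysis is kept as supportive, take the wait-list arm's pre-yoga re-assessment as its baseline, include arm as a factor, and drop the rule that pools according to baseline significance. Residual regression to the mean remains and should be stated.
5. Reconcile Phase three, Design and Treatment administration on whether wait-list participants must still meet the entry criteria before yoga, and report how many did not proceed.

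The cost is the rewording of two hypotheses and the follow-up analysis text, with minor changes to the analysis. No new data are needed. The price is a more modest claim about durability; a controlled claim at two months would need a control group kept untreated until that visit.

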### Exclusion criteria

Patients will be excluded from the study based on the following criteria:

• Intra-articular steroid injections within 4 weeks of screening.

• Treatment with any investigational agent within 8 weeks of screening or 5 half-lives of the investigational drug (whichever is longer).

• History of drug, alcohol, or chemical abuse within 6 months prior to screening.

• Any other disease, metabolic dysfunction, physical examination finding, or clinical laboratory finding giving reasonable suspicion that might affect the interpretation of the results or render the patient at high risk from treatment complications.

• Inability to comply with study and follow-up procedures.

• Currently pregnant.

• Previous practice of Iyengar yoga within the past three months.

• Inability to speak and understand English.

According to the Power/Sample Size calculations outlined below, we will recruit 35 patients each for the IYP and control conditions. After accounting for our projected attrition rate of 20%, we estimate there will be roughly 28 treatment completers in each condition. To accommodate 56 participants during the 36-month study period, we plan to conduct 4 initial IYP groups and 4 initial control groups, with approximately 8 patients in each group.

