### Sample Size Determination and Power Analysis

A power analysis was conducted to determine the appropriate sample size. Using a pre-test post-test for randomized groups, calculating power of the interaction of treatment by time, the sample size estimate is a total sample of 54, or 27 subjects per group (at a 0.05 significance level, 80% power for a medium effect size). We calculated a medium effect size given that our recent single-arm pilot study found an effect size of .46 (Cohen's d) for the HAQ, our arthritis-specific primary outcome measure. Assuming a 20% attrition rate that is consistent with our previous yoga studies, we will recruit 35 participants for each group (total n = 70).

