### Preliminary analyses

Once the data set has been cleaned and examined for skewness and missing data, exploratory data analyses will be conducted using univariate methods to describe the variables of interest and bivariate techniques to characterize their interrelationships within our sample. Continuous variables will be summarized over time in each group using means and medians and we will also report their range, interquartile range and standard deviations. Cross tabulated frequencies will be given for all discrete variables by group and time. Results from these descriptive analyses will be used to guide the primary analyses by providing information about potential problem measures (e.g., heavily skewed distributions) or problematic variable relationships (e.g., highly correlated predictors) and will help determine if transformations of some outcomes are possible in order to use parametric methods. We will test for baseline between-group differences in the outcome measures. Any variables found to vary significantly by group will be included as covariates in primary and secondary analyses. This will also serve to verify that the randomization was successful.

Missing data will be handled using multiple imputation [74] using the SAS routines PROC MI (20 imputations) and PROC MIANALYZE (to combine estimates). The imputation process is fostered by including additional variables (not part of the intended analytic model) that are highly correlated with variables that have missing data or that are associated with the probability that those variables have missing data. Such covariates (used in imputation only) will vary from analysis to analysis and their viability will be evaluated by preliminary analysis (e.g., zero-order correlations with variables with missing data) and their impact on the imputation model (e.g., change in standard errors of imputed variables). Multiple imputation has been shown to perform well with small samples [74].

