For ***Hypothesis 1***: The IYP will be safe, acceptable and feasible: more than 80% of subjects will complete the training program, we will examine the frequencies of drop-outs for the IYP and control groups. We will compare attrition rates between the groups; we will also compare demographic characteristics and baseline values of functioning between those who complete the protocol and those who do not. If drop-outs are random, then the results may be considered unbiased. If drop-outs are not random, we will comment on the direction and magnitude of potential biases.

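### The article gives conflicting rules for dropout in the primary outcomes, and the LOCF analysis cannot confirm a completer result

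*Protocol article*

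**What the plan says.** Three statements bear on participants who leave.

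- Preliminary analyses, general rule: "Missing data will be handled using multiple imputation". It names 20 imputations and auxiliary variables, and is not limited to any outcome or analysis.
- Primary analyses, closing paragraph: an additional intent-to-treat analysis of the primary outcomes is planned "to confirm our findings in completers by including all participants who enrolled in the study, using the last observation carry forward approach". Dropouts enter with the scores they gave before leaving.
- Preliminary analyses, paragraph on Hypothesis 1: attrition is compared between arms, and completers are compared with non-completers on demographics and baseline functioning. Then: "If drop-outs are random, then the results may be considered unbiased". If dropout is not random, the authors will comment on the direction and size of possible bias.

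The sample size also counts completers: "Assuming a 20% attrition rate that is consistent with our previous yoga studies, we will recruit 35 participants for each group", and "we estimate there will be roughly 28 treatment completers in each condition".

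**The concern.** If multiple imputation governed the primary repeated-measures ANOVA, dropouts would already be in it. There would then be no completer findings to confirm, and no need for a separate analysis to bring dropouts back. If completers govern, imputation has no stated role for outcomes lost to dropout. The intent-to-treat analysis fills the same missing scores by a different rule from the general one. As written, the rule for the primary test could be settled after the data are seen.

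The three rules answer differently when a fifth of participants leave. Completers are a subset formed after randomisation. LOCF fixes a dropout's change at zero after the last visit attended. For a person lost between post-treatment and the two-month visit, that means full maintenance, which is what Hypothesis 2 predicts.

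**Working it through.** **1. The plan's own figures.** Sample Size Determination gives "a total sample of 54, or 27 subjects per group" and 20% attrition. 27 / 0.8 = 33.75, so 34 per arm; 28 / 0.8 = 35. The stated 35 per arm is consistent, and 35 × 0.8 = 28 completers per arm. Overall, 70 × 0.2 = 14 dropouts and 56 completers. The 54 itself depends on an unstated pre-post correlation; nothing below uses it.

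**2. LOCF at post-treatment.** Only baseline precedes this visit. If a proportion p of an arm is lost, then

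LOCF mean change = (1 − p) × completer mean change + p × 0.

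With p = 0.2 in both arms, the LOCF group difference is 0.8 × the completer difference, whatever caused the dropout. A true 0.50 SD under random dropout becomes 0.8 × 0.50 = 0.40. With equal attrition the LOCF estimate therefore always has the same sign as the completer estimate and adds no information about those who left.

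**3. The three rules compared.** Large-sample simulation, 1,000,000 per arm. Assumptions: baseline and post-treatment SD 1; correlation 0.5 or 0.7 (none is given in the article); 20% dropout in each arm, random among controls; imputation by regression on baseline within arm. Ranges cover the two correlations.

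| Yoga dropout | True effect | Completers | LOCF | Imputation |
|---|---|---|---|---|
| Random | 0.50 | 0.50 | 0.40 | 0.50 |
| Driven by baseline score | 0.50 | 0.38 to 0.43 | 0.30 to 0.34 | 0.50 |
| Driven by poor response | 0.50 | 0.69 to 0.75 | 0.55 to 0.60 | 0.67 to 0.70 |
| Driven by poor response | 0 | +0.19 to +0.25 | +0.15 to +0.20 | +0.17 to +0.20 |

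The LOCF column is 0.8 times the completer column, as step 2 requires. How strongly dropout depends on response is an assumption. In SD of change, the spurious completer effect when 20% leave is 0.10 for weak dependence (logistic slope 0.5), 0.17 for slope 1, and 0.35 if exactly the worst fifth leave (normal density at the 20th percentile / 0.8 = 0.280 / 0.8).

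**4. LOCF at follow-up.** Take a true post-treatment gain of 0.50 that is wholly lost by two months.

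- All 20% lost before post-treatment: LOCF gain 0.40, then 0. Retained: 0%.
- 10% lost before and 10% after: post 0.9 × 0.50 = 0.45; follow-up 0.1 × 0.50 = 0.05. Retained: 11%.
- All 20% lost after: post 0.50; follow-up 0.2 × 0.50 = 0.10. Retained: 20%.

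For the standard error, take n = 70, correlation 0.7, a true loss of 0.30 and 20% lost after post-treatment. The variance of change is 2 × (1 − 0.7) = 0.60.

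- Observed cases: estimate 0.30, SE = √0.60 / √56 = 0.103.
- LOCF: estimate 0.8 × 0.30 = 0.24; variance = 0.8 × (0.60 + 0.09) − 0.24² = 0.494; SE = √(0.494 / 70) = 0.084.

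**5. The check for random dropout.** 14 dropouts against 56 completers, difference 0.5 SD, two-sided 5%: noncentrality = 0.5 × √(14 × 56 / 70) = 1.67 on 68 degrees of freedom, power 0.38. Baseline variables also cannot show dropout driven by later response.

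**The case against.** The strongest defence is that imputation, a completer analysis and an intent-to-treat check can coexist, and that ranking them is commonly left to an analysis plan that is not shown here. The absence of a ranking would be no finding. The point survives because the article does more than stay silent: it states one rule for missing data without restriction and then fills missing primary outcomes by another.

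A reader might infer three stronger things that the documents do not support.

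- *That completers are the declared primary analysis.* The wording points that way, but no sentence says so. If the general rule governs, the primary test uses imputation.
- *That bias is built in.* Under random dropout the completer estimate is correct (0.50 of 0.50). Otherwise the direction is open. The article plans the same 20% attrition in both arms, offers make-up classes and gives controls the programme later, so unequal or response-driven dropout is a risk, not a fact.
- *That maintained gains are created by the imputation.* The artefact belongs only to the LOCF analysis and only to people lost after post-treatment. Estimate and standard error also shrink together: 0.24 / 0.084 = 2.86 against 0.30 / 0.103 = 2.91, so a loss is detected almost as readily. What is distorted is the size.

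It is also fair that at post-treatment LOCF pulls the completer estimate towards zero, which works against Hypothesis 2; that the article promises to discuss bias if dropout is not random; and that this is an exploratory study. Finally, imputation on baseline alone barely reduces bias from response-driven dropout (+0.17 to +0.20 against +0.19 to +0.25). That objection stands and shapes the fix.

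**Conclusion.** The concern holds in limited form. The conflict between the two sections is on the page and needs no assumption. LOCF is a poor confirmation whatever the dropout mechanism: it gives 0.40 for a true 0.50 under random 20% dropout, and when poor responders leave yoga it errs in the same direction as completers. Its follow-up distortion is bounded at about 20% of a true loss at planned attrition, is zero if all dropout comes before post-treatment, and understates the standard error in that analysis only. Bias in a completer estimate is conditional on non-random dropout; the figures in step 3 rest on assumed correlations and mechanisms and show possible size, not expected size. The sentence treating random dropout as sufficient for unbiasedness cannot be acted on, since a comparison with 38% power does not establish randomness.

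**What to change.** - In Primary analyses, state that the primary analysis includes all randomised participants in their assigned arm, using the multiple imputation already described, with treatment arm, baseline scores and summarised weekly ratings (pain, fatigue, anxiety, depression) in the imputation model.
- Label the completer analysis supportive.
- Delete LOCF. Replace it with a simple delta-adjusted sensitivity analysis: make the imputed scores of yoga dropouts worse by a stated range of amounts and report where the conclusion changes. With 20% yoga dropout, a shift of δ moves the estimate by 0.2 × δ, so the residual bias of 0.17 to 0.20 SD corresponds to δ of about 0.85 to 1.0 SD.
- Delete the sentence that treats results as unbiased when dropout is random. Keep the descriptive comparison of attrition for Hypothesis 1.

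The cost is a few sentences and a little programming, with no new measurements. The limit is the small imputation model: with about 28 observed patients per arm the weekly ratings must be summarised rather than entered week by week, and they help only for weeks in which a participant was still reporting.
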